#### **13.2. Sample library**

Sample library will be taken at W0 and W52. The blood volume taken will be 17 mL (8,5 mL x 2). The sampling will be performed within 7 days before the corresponding visit and sent to the centralised laboratory with other tubes.

The sample library will be kept at minus 70 C° in the centralised laboratory.

At the end of the study, the Scientific Committee will decide which tests should be performed.

## 14. STATISTICS

### 14.1. Statistical analysis

A Statistical Analysis Plan will be written after finalising the protocol and definitively completed before breaking the blind. These specifications will detail the implementation of all the planned statistical analyses in accordance with the principal features stated in the protocol.

#### 14.1.1. Evaluation criteria

##### Efficacy criteria

- Main criterion :

- ✓ HbA1c (%):
  - Main analytical approach: Change from baseline to last post-baseline value

- Secondary criteria

- ✓ LDL cholesterol (mmol/L)
- ✓ Fasting plasma glucose (mmol/L)
- ✓ Fasting plasma insulin (pmol/L)
- ✓ HOMA-IR
- ✓ Other fasting serum lipids: total cholesterol (mmol/L), HDL cholesterol (mmol/L), triglycerides (mmol/L), non-HDL cholesterol (mmol/L), Apo A1 (mmol/L), Apo B (mmol/L) and LDL particle size
- ✓ hsCRP (mg/L)
- ✓ Waist circumference (cm)

##### Safety criteria

- ✓ Adverse events (including oedemas and cardiovascular events)
- ✓ Hypoglycaemia
- ✓ Physical examination (weight, BMI, blood pressure and heart rate)
- ✓ 12-lead ECG and echocardiography
- ✓ Centralised biochemistry (including lactic acid (mmol/L)), haematology and NT-proBNP (pg/mL)

#### 14.1.2. Statistical elements

The type one error of the statistical analyses will be set at 5% in two tailed situation and 2.5% in one tailed situation.

The following descriptive statistics will be provided depending on the nature of variables:

Quantitative variable: number of observed values, mean and standard deviation, minimum and maximum, and if necessary median, first and third quartiles.

Qualitative or ordinal variable: number and percentage by class.

### **14.1.3. Analysis sets**

#### **Randomised Set (RS)**

This set will correspond to all randomised patients.

#### **Safety Set (SS)**

This set will correspond to patients who received at least one dose of study treatment.

#### **Full Analysis Set (FAS)**

Based on the intention-to-treat principle, this set will correspond to randomised patients who have taken at least one dose of study treatment and who have at least one baseline value and one post-baseline value of HbA1c.

#### **Per Protocol Set (PPS)**

This set will correspond to patients of the Full Analysis Set with a correct treatment compliance, with a long term measure of HbA1c and without relevant deviation(s) which could affect the evaluation of HbA1c (primary criterion).

Based on the actual deviations, the criteria for exclusion of patients from the different data sets will be specified and updated if necessary before breaking the blind.

Different subgroups will be defined according to age, baseline value of HbA1c according to EMEA guideline on diabetes (CPMP/EWP/1080/00, 30 May 2002 or new release version).

### **14.1.4. Statistical methodology**

#### Study Outcome

Characteristics of patients including demography, prognostic factors, baseline values of assessment criteria will be described by treatment group and overall for the RS.

Treatment duration, duration of exposure to treatment, global treatment compliance (test drugs and sulfonylurea), status of patients and reason for withdrawal, protocol deviations, concomitant treatments will be described by treatment group and overall for the RS.

Main characteristics of patients will also be described for the SS, the FAS and the PPS.

#### Efficacy

Efficacy analyses will be carried out primarily on the FAS and secondarily on the PPS.

- Main criterion

#### Main analysis:

The main analysis will test the non-inferiority of benfluorex to pioglitazone on the change from baseline value to last post-baseline value using a general linear model studying treatment effect with baseline and country as covariates. The estimate of treatment difference, its standard error and its 95% confidence interval will be provided.

The non-inferiority limit will be set at 0.4%. If non-inferiority is demonstrated, the superiority of benfluorex to pioglitazone will be tested.

In case of sufficient number of centers with minimal number of patients, a mixed model with center as random factor will be used as sensitivity analysis.

#### Secondary analyses:

- Secondary criteria

The same model as for the main analysis will be performed (estimate of treatment difference, standard error and 95% confidence interval will be provided). A non-parametric approach could be used if necessary.

For LDL cholesterol, superiority of benfluorex to pioglitazone will be tested.

The responder rates on main criteria will be compared using a definition of responders to be defined in the statistical plan (current definition at time of analysis).

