| Methodology:
- randomised (by IVRS), double-blind, double-dummy, parallel group, comparative (benfluorex versus pioglitazone) study,
- with stratification at baseline on country and HbA1c $\leq 8\%$ or $> 8\%$ .                                                                                                                                                                                                                                                                                                                                                                                                                                                                                                                                                                                                                              |                                                                |                                          |
| Number of participants:
Planned: 950 patients analysed in the Full Analysis Set (475 by group), 1000 included with at least 500 patients with baseline HbA1c $> 8\%$ .                                                                                                                                                                                                                                                                                                                                                                                                                                                                                                                                                                                                                                                                              |                                                                |                                          |

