**Primary efficacy criterion: HbA1c (%)**  
Main analytical approach: change from baseline to the last post-baseline value  
The main analysis will test the non-inferiority of benfluorex to pioglitazone on the change from baseline value to last post-baseline value using a general linear model studying treatment effect with baseline and country as covariates. The non-inferiority limit will be set at 0.4%.  
**Other efficacy criteria** will be analysed with the same model.

|                                                                                                          |                                                                                    |                                          |
|----------------------------------------------------------------------------------------------------------|------------------------------------------------------------------------------------|------------------------------------------|
| Name of the sponsor: I.R.I.S.
[name]
[name] - FRANCE | Individual Study Table
Referring to Part
of the Dossier | (For National Authority Use only) |
| Name of Finished Product:
Trade Name (specify the country)                              | Volume:                                                                     |                                          |
| Name of Active Ingredient:
benfluorex
(S00780)                                | Page:                                                                       |                                          |

Safety analysis:

Descriptive statistics will be provided for adverse events (including cardiovascular events and oedemas), episodes of hypoglycaemia, laboratory tests, vital signs (blood pressure, heart rate, weight), ECG and echocardiography abnormalities.

Other analysis: Economic balance.

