### 8.3. Measures to minimise bias

This is a multicentre, international, randomised, double-blind, double-dummy, parallel group study.

The following methods will be used to protect the blinding vis-à-vis the participants and the investigators:

- The tablets of benfluorex and benfluorex placebo will have the same aspect (size, colour) and taste. The capsules of pioglitazone and pioglitazone placebo will also be strictly identical.
- All the packaging (blisters, boxes, labels) will be strictly identical between the two treatment groups.
- In each group, patients will receive a product and the placebo of the other drug (in the benfluorex group: 3 tablets of benfluorex and 1 capsule of pioglitazone placebo will be administered per day, and in the pioglitazone group: 3 tablets of benfluorex placebo and 1 capsule of pioglitazone will be administered per day).
- The investigator will provide the CRO in charge of IVRS with all data needed for the evaluation of the dose level increase/decrease. The CRO in charge of IVRS will be responsible for the management of dose level increase/decrease according to the treatment group following the specific procedures described below.
- Sealed code list will be available at the I.R.I.S. emergency desk. No envelop with the code will be available in centres. The Adjudication Committee is blinded. The management of the blinding system is described in the section section 8.4.3. “*Management of blinding systems*”.
- Treatments will be allocated under the responsibility of the CRO responsible for the **Interactive Voice Response System (IVRS)** by non-adaptative, centralised, balanced (1:1), stratified randomisation, according to country and HbA1c ( $\leq 8\%$  or  $> 8\%$ ) at W0.

The structure responsible for designing the randomisation lists will be the Biometrics Direction of I.R.I.S..

All the efficacy and safety laboratory measurements will be analysed by a **central laboratory** in blind of the treatment allocated.

Circumstances under which the code is to be broken are described in section 8.4.3. “*Management of blinding systems*”.

All the echocardiographies will be assessed by a central reading structure in blind of the treatment assignment.

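### The model fixed for the secondary criteria leaves out the HbA1c randomisation stratum, so their standard errors may be slightly too wide

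*Protocol*

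**What the plan says.** Section 8.3 of the protocol describes "non-adaptative, centralised, balanced (1:1), stratified randomisation, according to country and HbA1c", with HbA1c split at 8% at W0. Section 10.2 repeats this, and the synopsis gives the design as "with stratification at baseline on country and HbA1c" with the same cut.

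Section 14.1.4 tests the primary criterion, change in HbA1c, "using a general linear model studying treatment effect with baseline and country as covariates". For the secondary criteria it states: "The same model as for the main analysis will be performed". An estimate, a standard error and a 95% confidence interval are promised for each of them, and LDL cholesterol also gets a superiority test. The synopsis agrees that the other efficacy criteria "will be analysed with the same model". The only stated alternative is "A non-parametric approach could be used if necessary", which does not bring in the stratum either. Nowhere does the protocol place the HbA1c stratum in a model.

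**The concern.** For HbA1c, baseline plus country covers both stratification factors, because baseline HbA1c is the variable from which the stratum is cut. When the same sentence is carried over to LDL cholesterol, FPG, insulin, HOMA-IR, other lipids, hsCRP and waist circumference, baseline most naturally becomes the baseline of that criterion, and HbA1c leaves the model. The text does not say this outright. Read the other way, with baseline meaning HbA1c throughout, the model would keep the stratum information but lose the criterion's own baseline. Either way one relevant covariate is missing.

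Stratified allocation removes chance imbalance in the stratum, and so removes that source of variation from the treatment estimate. A model without the stratum still counts the variation in its residual. If the stratum is prognostic, the model-based standard error then exceeds the true one. What is at stake is some precision and power on the secondary criteria, including LDL superiority, which section 7 names as the main secondary objective.

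**Working it through.** **The plan's own figure.** The protocol states no standard deviation, effect or power for any secondary criterion. Its only sample size is for HbA1c (section 14.2): SD 1.5%, margin 0.40%, true difference up to 0.05%, one-sided 2.5%, power 95%. Per group, n = 2 × (1.960 + 1.645)² × 1.5² / (0.40 − 0.05)² = 477.4, so 478 by the normal approximation and 479 by the exact noncentral t. The stated 479 reproduces and does not depend on this point.

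**Inputs**
- Strata: country and W0 HbA1c ≤ 8% or > 8%, 1:1 (sections 8.3 and 10.2, synopsis).
- Secondary model: treatment, baseline, country (section 14.1.4, synopsis).
- Two-sided 5% level (section 14.1.2).
- r, the partial correlation of the stratum with the change in the criterion, given that criterion's own baseline and country. The documents do not give it, so it is an assumption shown as a range.

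**Formulas.** If the residual variance without the stratum is s², the true variance of the treatment difference under stratified allocation is proportional to s²(1 − r²). Hence:
- ratio of reported to true standard error: k = 1/√(1 − r²)
- actual two-sided error: 2 × [1 − Φ(1.960 k)]
- power, for a test with 80% power when the stratum is modelled: 1 − Φ(1.960 k − 2.802)

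For example, at r = 0.2: k = 1/√0.96 = 1.0206, 1.960 × 1.0206 = 2.000, error 4.55%.

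| Assumed r | SE too wide by | Actual two-sided error | Power (80% if adjusted) |
|---|---|---|---|
| 0 | 0% | 5.00% | 80.0% |
| 0.1 | 0.5% | 4.89% | 79.7% |
| 0.2 | 2.1% | 4.55% | 78.8% |
| 0.3 | 4.8% | 3.99% | 77.2% |

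The 80% is only a reference point; the protocol plans no power for these criteria.

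**Simulation check.** The settings were 960 patients, five countries, two strata of equal expected size, permuted blocks of four within country by stratum (the block size is assumed) and 3000 runs per setting. Mean model standard error without and with the stratum was:
- r = 0.1: 0.0649 and 0.0646 (ratio 1.005 from unrounded values)
- r = 0.2: 0.0659 and 0.0646 (ratio 1.021)
- r = 0.3: 0.0677 and 0.0646 (ratio 1.048)

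These ratios match k. The empirical SD of the estimate was practically the same under both models in each setting (for r = 0.2, 0.0636 in both). So the true precision is unchanged and only the reported standard error is too large. The simulated rejection rates have a Monte Carlo error of √(0.05 × 0.95/3000) = 0.4 percentage points, too coarse to confirm error rates this close to 5%. The error column above rests on the formula.

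**The case against.** The strongest reply is that nothing in the documents shows a loss. A reader might infer that the standard errors of all secondary criteria are too wide. That does not follow: at r = 0 there is no excess, and no value of r is given. For FPG, the criterion's own baseline already carries part of the HbA1c information, and section 9.3 restricts entry to HbA1c above 7% and up to 10%, which limits what a split at 8% can add. For LDL cholesterol, the one secondary criterion with a declared superiority test, a weak association is the reasonable expectation. This stands, and it limits the point to a conditional and small one.

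A reader might also infer that the responder comparison is faulty, since reaching an HbA1c target depends on the starting value. The protocol does not support that either. Section 14.1.4 leaves the responder definition to the statistical plan and fixes no test or model for the comparison, so there is no stated error to correct.

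Finally, the covariates could be called implementation detail for the SAP. That does not dispose of the point. The protocol itself names the covariates and extends them to the secondary criteria, and section 14.1 binds the SAP to the principal features stated in the protocol. This is a stated model that does not match the stated randomisation.

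**Conclusion.** The point holds in a limited form. On the natural reading of baseline, the model fixed for the secondary criteria omits one of the two stratification factors. The consequence depends on how far the HbA1c stratum predicts each change beyond the criterion's own baseline and country. Over an assumed partial correlation of 0 to 0.3, the reported standard error is 0% to 4.8% too wide; at 0.1, which would be plausible for LDL cholesterol, the excess is 0.5%. The direction is always conservative. The treatment estimates are not biased, no false claim of superiority becomes more likely, and the primary non-inferiority analysis is untouched. This is a minor matter of efficiency and does not threaten the validity of the trial.

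**What to change.** In section 14.1.4 and in the synopsis, state that each secondary criterion is analysed with a general linear model with treatment, the baseline value of that criterion, country and the W0 HbA1c stratum (≤ 8% / > 8%) as covariates. Continuous baseline HbA1c may replace the stratum. The same sentence settles what baseline means. Leave the primary model as it is, since it already contains baseline HbA1c and country.

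The cost is one sentence in each place and one degree of freedom among about 950 analysed patients. The variable is already held for randomisation, so no new data or patients are needed. The change should be made before the blind is broken. As advice for the SAP only, the responder comparison can be adjusted for the same strata when its method is chosen.

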## **7. STUDY OBJECTIVES AND PURPOSE**

The purpose of this study is to compare the efficacy and the safety profile of benfluorex and pioglitazone in type 2 diabetic patients, not optimally controlled on sulfonylurea, over 1 year.

The primary objective will be to demonstrate the non-inferiority of the combination sulfonylurea plus benfluorex compared to the combination sulfonylurea plus pioglitazone on the evolution of HbA1c.

Both benfluorex and pioglitazone will be administered at optimal dosage for the treatment of type 2 diabetic patients insufficiently controlled on sulfonylurea monotherapy.

The main secondary objective is to demonstrate the superiority of benfluorex combined with sulfonylurea compared to pioglitazone combined with sulfonylurea on LDL cholesterol level.

The other secondary objectives will be to evaluate and compare over 1 year both combination therapies on the following:

- Fasting Plasma Glucose evolution.
- Insulin Resistance assessed by homeostatic model assessment (HOMA-IR).
- Cardiovascular risk profile.
- Safety and acceptability.
- Cost of the two treatments through an economic balance.

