**14.2. Determination of sample size**

Sample size is estimated on the change from baseline to last value of HbA1c, to evidence a non-inferiority of benfluorex group as compared to pioglitazone group, using the one-sided Student t test at 2.5% type I error.

For a 1.5% standard deviation and a 0.40% clinical equivalence limit, 479 subjects per group to analyse in the Full Analysis Set are necessary to show a non-inferiority between groups if the true difference is equal to zero ( $\pm 0.05\%$ ), with at least a power of 95%.

Taking into account the Full Analysis Set definition (975 patients to be analysed), about 500 patients per group will be included.

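### LDL superiority is worded as a claim to demonstrate, but it is neither tied to HbA1c non-inferiority nor ordered against HbA1c superiority, so the error rate across the claims is not held at 2.5%

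*Protocol*

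**What the plan says.** Four places in the protocol bear on this.

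- **Objectives (section 7).** "The main secondary objective is to demonstrate the superiority of benfluorex combined with sulfonylurea" compared with the pioglitazone combination, on LDL cholesterol. The study summary and section 6 also word LDL superiority as something to demonstrate, and section 11.2 lists LDL as the first secondary criterion.
- **Error level (section 14.1.2).** "The type one error of the statistical analyses will be set at 5% in two tailed situation and 2.5% in one tailed situation". No split, adjustment or hierarchy is given.
- **HbA1c (section 14.1.4, main analysis).** Non-inferiority is tested first, and then "If non-inferiority is demonstrated, the superiority of benfluorex to pioglitazone will be tested". This is an explicit gate.
- **LDL (section 14.1.4, secondary analyses).** "For LDL cholesterol, superiority of benfluorex to pioglitazone will be tested". No condition is attached and no place in an order is given.

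No other part of the protocol ties the LDL test to the HbA1c tests.

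**The concern.** The protocol opens three routes to a favourable statement about benfluorex: HbA1c non-inferiority, HbA1c superiority and LDL superiority. Only the second is tied to the first. The LDL test stands outside that chain at full level, although it is the only other claim that the objectives say is to be demonstrated.

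Two things follow from the text as it stands. LDL superiority could be declared in a trial that had failed its primary objective. And even when non-inferiority is met, two superiority tests run side by side at 2.5% each, so the chance that at least one false claim is made can exceed 2.5%. Section 20 says the final report may support a registration request, so the error rate over the set of claims matters.

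**Working it through.** **Inputs from the protocol.** Margin: "The non-inferiority limit will be set at 0.4"% (section 14.1.4). Test: "using the one-sided Student t test at 2.5% type I error" (section 14.2). Variability: "For a 1.5% standard deviation and a 0.40% clinical equivalence limit" (section 14.2). Planning difference: "if the true difference is equal to zero", with a tolerance of 0.05% (section 14.2). 479 per group in the Full Analysis Set, power at least 95%, allocation 1:1.

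**Reproducing the plan's own figure.** With the true difference 0.05% against benfluorex, the normal formula gives

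n = 2 × 1.5² × (1.960 + 1.645)² / (0.40 − 0.05)² ≈ 478 per group.

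The exact t calculation gives 479, with power 95.03%. The stated size is reproduced. At 479 per group the chance of showing non-inferiority is 98.5% at zero difference and 95.0% at 0.05%.

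**Where a false claim is possible.** Take no true LDL effect, so an LDL claim is false with probability 0.025. Write d for the true HbA1c difference against benfluorex. The standard error is 1.5 × √(2/479) = 0.0969.

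- For 0 ≤ d < 0.4, non-inferiority is true and HbA1c superiority is false. The chance of a false HbA1c claim is p = P(Z > 1.960 + d/0.0969).
- For d ≥ 0.4, non-inferiority itself is false. The chance of a false HbA1c claim is p = P(Z > 1.960 + (d − 0.4)/0.0969).
- With independent tests, P(at least one false claim) = 1 − 0.975 × (1 − p).

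| True HbA1c difference d (%) | p | At least one false claim |
|---|---|---|
| 0 | 0.0250 | 4.9% |
| 0.025 | 0.0133 | 3.8% |
| 0.05 | 0.0066 | 3.1% |
| 0.10 | 0.0014 | 2.6% |
| 0.20 to 0.35 | below 0.0001 | 2.5% |
| 0.40 | 0.0250 | 4.9% |
| 0.50 | 0.0014 | 2.6% |

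The two peaks are 1 − 0.975² = 4.94%.

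**Correlation.** The protocol gives no correlation between the HbA1c and LDL test statistics, so a range is assumed. At the peaks the rate is 4.94% at correlation 0, 4.76% at 0.3 and 4.54% at 0.5. It cannot exceed 2.5% + 2.5% = 5.0% under any correlation.

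**LDL claim after failed non-inferiority.** At d = 0.4 with independent tests: 0.975 × 0.025 = 2.4% of trials. At d = 0 it is about 0.015 × 0.025 = 0.04%.

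**Possible repairs, by simulation** (4 million draws, 479 per group, independent tests, no LDL effect):

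| Rule | d = 0 | d = 0.4 |
|---|---|---|
| As written | 4.9% | 4.9% |
| LDL gated on non-inferiority only | 4.9% | 2.5% |
| Non-inferiority, LDL, HbA1c superiority | 2.4–2.5% | 2.5% |
| Non-inferiority, HbA1c superiority, LDL | 2.5% | 2.5% |

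A gate on non-inferiority alone leaves the peak at d = 0. An order between the two superiority tests is needed as well, and either order controls the error. They differ in what they cost the LDL claim. With HbA1c superiority second and d = 0, that step fails 97.5% of the time and LDL is never reached. With LDL second, it is blocked only when non-inferiority fails: 1.5% at d = 0 and 5% at d = 0.05.

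**The case against.** The strongest case on the other side has four parts.

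**The statistical analysis plan may settle this.** Section 14.1 leaves implementation to a plan completed before unblinding, and testing order is often set there. That plan has not been seen and may contain an order. But section 14.1 also says the plan follows the principal features stated in the protocol. The protocol itself fixes the error level, fixes a gate for one superiority claim and states a second claim to be demonstrated outside that gate. The gap lies in what the protocol does fix.

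**A secondary claim is ordinarily read after the primary.** This is a fair reading, and it would remove the peak at the 0.4% margin. It does nothing at zero difference, where non-inferiority passes about 98.5% of the time and the rate stays at about 4.9%.

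**HbA1c superiority is not among the listed objectives.** That is true, and a sponsor could settle the matter by declaring that test supportive only. The protocol does not do so. It plans the test at the same level as the others.

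**The size is easily overstated.** This stands. A reader might infer that the LDL test has no controlled error, that the primary test is inflated, or that the false-claim rate simply doubles. The documents support none of these. Section 14.1.2 gives the LDL test its own 2.5%. The non-inferiority test comes first and is unaffected. Near-doubling occurs only close to a true HbA1c difference of 0 or 0.4%. Nor would following the order of the text leave the error uncontrolled: it would hold it at 2.5% and cost only power for LDL.

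**Conclusion.** The point holds as a gap in control across the claims. With no LDL effect and independent tests, the chance of at least one false favourable claim is up to 4.9% one-sided instead of 2.5%, at a true HbA1c difference of 0 (the planning value) or at the margin. At the 0.05% tolerance used for the sample size it is about 3.1%, and over most of the range between it is about 2.5%. The text also permits an LDL claim after a failed primary objective.

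These figures rest on the protocol's standard deviation of 1.5% and 479 per group, and on HbA1c superiority counting as a claim. If LDL truly differs in benfluorex's favour, an LDL claim is not false and the excess disappears. The correction is worth making in the protocol because it is nearly free, but the point does not undermine the primary analysis.

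**What to change.** State one fixed sequence in section 14.1.4, each step at 2.5% one-sided, stopping at the first failure:

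1. HbA1c non-inferiority at the 0.4% margin.
2. LDL superiority.
3. HbA1c superiority.

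Put LDL second because section 7 names it as the main secondary objective. State that the remaining secondary criteria are reported as estimates with 95% confidence intervals, which section 14.1.4 already provides for, and carry no confirmatory claim. Repeat the sequence in the statistical analysis plan before unblinding.

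The cost is one paragraph in each document, with no change to the level of any test and no additional patients. Two claims become conditional. LDL cannot be claimed if non-inferiority fails (about 1.5% of trials at zero difference, 5% at 0.05%), and HbA1c superiority cannot be claimed if LDL superiority is not shown.
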